## Study Logistics

### Community Mobilization and Sensitization Activities

Community mobilization and sensitization activities will be conducted prior to the implementation of activities. These activities will follow similar methods as deployed prior to Zambia’s MIS and would prepare communities for the reactive responses, including collection of a finger stick blood sample for parasite and antibody testing. A general information letter and accompanying flyer will be prepared for participating districts and local communities. These documents will include information about the purpose, procedures, and importance of household participation. Further, a radio spot will be developed and aired on local community radio stations with service areas matching the selected communities. The radio spot will serve to introduce the activity and encourage participation. PATH already has local knowledge and key relationships with leaders in the study areas. Thus, existing communication channels with key leaders e.g. chiefs and headmen, will be leveraged to share information about the benefit of the upcoming research activities.

### Incentives

Incentives for CHWs (standard Step D):

- Bicycles
- Basic feature phones available as an incentive / trade-in for completion of Step D monthly reports
- Talk time sent automatically as an incentive for completion of Step D monthly reports. Value will reflect the timeliness of the reporting
- CHW packs - backpack with sharps disposal container

## Data Management

Data collected during the three surveys and the reactive research responses will be recorded on an android smartphone or tablet. This personally identifiable data will be securely transferred over the telephone network, as soon as a data connection is available, to a central server controlled by PATH. Access to the server will be password protected and secured according to best practice. Local copies of the database will be secured in password protected files on password protected computers.

Prior to analysis, data will be de-identified with the exception of geo-location codes which are necessary for specific per-protocol analyses, the absence of individual identifying information will protect subject confidentiality.

All paper records, consent forms and biological specimens will be stored in a locked location.

## Personnel

### Survey team

Teams consisting of the individuals listed below will be recruited to perform the endline survey. Training will occur in consultation with and oversight by National Malaria Control Program representatives.

- Local CHW to provide local knowledge of area and community residents
- Sample collector with previous experience collecting DBS
- Enumerator trained to enter data electronically
- Driver

### Standard CHW Response (RFTAT / RFDA)

CHWs will perform all required activities as per existing Step D documentation through the NMCP (Appendix 1).

### Research Response (RFTAT / RFDA)

Community health workers will inform the research team through an SMS text message upon detecting a confirmed incident malaria case. The research team will then determine whether to accompany the CHW on the reactive response based on the location of the incident case, ability to respond and number of responses previously performed in that area. Each response team will consist of three individuals:

- A sample collector for dried blood spots
- An enumerator to administer surveys and input data into the phone / tablet
- A supervisor to co-ordinate responses and support sample and data collection needs as required

Each research team will have access to a hired 4x4 vehicle as required as well as a project purchased motorbike.

It is anticipated that a total of four research teams will be required. Teams will be based in locations according to the geographical spread of the health centers. Each team will be able to respond to either arm (RFTAT / RFDA) to maximize flexibility in the workforce.

## Sample Analysis Assays

Samples collected during this trial will be stored in a plastic bag with silica gel before transport to Lusaka where they will be put in a freezer. All samples will be analysed at the National Malaria Control Centre, Zambia. A subset of samples i.e. those enrolled in the HS RDT analysis (maximum 3,000 samples) will be sent outside the country to the PATH laboratory (Seattle, Washington, USA) for additional analyses e.g. *Pf* HRP2 Quansys Q-plex ELISA testing (Logan, Utah; Q-plex ELISA) and *Pf* HRP2/3 deletion PCR, as these analyses cannot currently be performed in country. It is anticipated that DBS specimens will be shipped to PATH every 3-6 months once an MTA has been approved. Samples will be stored for a maximum of three years from the completion of the study.

### PCR analysis for presence of Plasmodium falciparum

DNA will be extracted from dried blood spots collected during this trial and tested for the presence of *P. falciparum* DNA using a sensitive nested PCR to the multi-copy locus, 18s rRNA, or other target as appropriate

^44,45^.

### Genotype analysis on positive samples

PCR positive *P. falciparum* samples will be genotyped by molecular barcode

^46^. Depending on the genetic diversity of the samples all or a subset of the 24 SNPs will be employed to generate a unique barcode for each parasite. If mixed infections consist of a high multiplicity of infection (MOI) i.e. they contain a large number of different parasite genomes, it may be necessary to increase the system resolution by moving to a 96-SNP based system.

### Serology

Serology on all samples collected during the endline survey will be conducted for estimates of both long (e.g. AMA-1) and short-term exposure antigens, recent parasite transmission (Csp), as well as cumulative exposure to *Anopheles* mosquitoes (salivary peptides).

## Challenges and Limitations

### False Positive Test Results

As incidence reduces, the positive predictive value of RDTs decreases (Figure 8). This means that as malaria prevalence approaches zero, the proportion of positive RDT results that will be false positive increases. We will measure the positive and negative predictive values of the RDT by comparing the results to detection of asexual stage parasites by PCR.

[figure not shown]

Figure 8 – Predictive value of a positive or negative RDT result across a range of malaria prevalence. Figures are calculated assuming a diagnostic test sensitivity and test specificity of 95% each.

### Adequate RDT and ACT Supplies

To ensure that there are no stock outs of RDTs or ACTs, commodity supply will be closely monitored through the routine reporting of health center (Step 1) data in DHIS2. A constant supply of commodities to ensure the ability to produce an unbiased estimate of the effectiveness of the interventions will be necessary. To that end, 3 months’ supply of RDTs and ACTs will be procured specifically for this project and will be retained to act as an emergency reserve for the health center catchment areas.

# Ethical Issues

Community surveillance using the Step D, test and treat strategy (control arm) has already been implemented throughout the majority of Southern Province and is the standard of care in Zambia. Focal drug administration for malaria control has not yet been implemented in Zambia although multiple examples exist around the world.

There may be physical risks to the participants/respondents and those receiving the intervention and the surveys associated with a finger stick from blood drop collection, but they are not considered more than minimal. Lancets or needle sticks are potentially, but only temporarily, painful. The risk to data collectors of needle sticks will be minimized by training, use of sterile lancets and proper disposal. This protocol will be reviewed by Western Institutional Review Board and the University of Zambia Institutional Review Board.

## Adequacy of protection against risks

We will administer an informed written consent and assent form in English or the local language as required by the participant. Table 4 outlines the exclusion criteria, inclusion ages and consent / assent forms that will be administered. For the household survey, written consent for participation in the survey and intervention will be provided by an individual who is at least 18 years of age according to the laws of Zambia. These forms will be read and explained or will be given to participants to read themselves and will include a full description of voluntary participation, the right to withdraw from the study at any time and the right to not answer any question. The forms will also address the risks, benefits and purpose of the intervention and study, including what we hope to learn. For individual’s ≥1 month and less than 18 years of age, consent will be sought from the head of household or parent/household guardian above age 18. For children greater than six years and less than 18, oral assent will be sought from the child. We will train all interviewers extensively on the consent and assent procedures. Checks in the field by the project team, including observation of a reactive response, assessment of completed consent statements and questioning of the interviewer will ensure the consent process is strictly followed. The confidentiality procedures (listed in section 2.11 on p33) are designed to meet all contingencies so that the privacy of the participants is preserved.

| **Study/intervention data collection** | **Exclusion** | **Inclusion Ages** | **Consent/Assent** |
| --- | --- | --- | --- |
| **Endline Survey** | < 1 month or >15 years of age | ≥1 month and <6 years old | Adult Consent (Appendix 3) |
|  |  | 6-<15 years old | Oral assent (Appendix 19) |
| **RFTAT intervention** | Severe malaria patients, First trimester pregnant women, < 1 month of age | ≥3 months old | DHAP Consent (Appendix 11) |
| **RFDA intervention** | Severe malaria patients, First trimester pregnant women, < 3 months of age, individuals contraindicated for DHAP | ≥3 months old  ≥1 month old | Oral Assent 6-17 years (Appendix 16) |
|  |  |  | Reactive research response (Appendix 8) |
| **Research around reactive responses for RFTAT and RFDA** | < 1 month of age | ≥1 month old | Oral Assent 6-17 years (Appendix 16 |
|  |  |  |  |

Table 4 - Summary of inclusion / exclusion criteria and consent/assent forms. * RFTAT with AL represents current standard of care so consent / assent will not be required.

The development of drug resistance has been linked to the administration of therapeutic doses of antimalarials

^11^. Our proposed strategy to reduce the risk of the development of drug resistance includes:

- Directly observed treatment of the first dose of DHAP during all reactive responses
- In research responses, the team will additionally:
  - Check blister packs on day 3 to ensure that the second dose was taken
  - Directly observed treatment of the third dose of DHAP on day 3

Our proposed strategy to reduce risks associated with finger sticks includes:

- To clearly explain the procedures to each individual or caretaker so that they understand the transient pain associated with collection of finger prick blood samples and the extremely low risk of infection.
- To use specially trained and supervised fieldworkers who will be able to answer commonly asked questions.
- To specially train fieldworkers to collect and handle biological specimens and ensure that all data entry personnel are trained on confidentiality and safety issues, as well as on informed consent procedures. This includes special training for all team members on universal precautions for handling biological specimens.

DHAP has been approved by the Zambian Ministry of Health as the new alternate first-line standard of care drug for the treatment of uncomplicated malaria in Zambia. AL is also the first-line treatment for uncomplicated malaria and is widely available. A new Cochrane Review (2014) has shown that studies comparing DHAP to other antimalarials to be safe, effective and well-tolerated by individuals

^47^. DHAP is a combination of two antimalarial drugs (dihydroartemesinin and piperaquine). Dihydroartemesinin has been associated with the following: prolonged QT intervals, falciparum malaria, influenza, cough, fever, abnormal cardiac conduction, necrotizing enterocolitis in foetus or new-borns, leukocytosis, neutropenia, thrombocytopenia, hepatitis and seizure. The risk of DHAP is assumed similar to that of AL, the current widely available national first line treatment for uncomplicated malaria.

Adverse reactions to both RFTAT with AL and RFDA with DHAP will be assessed 3 days following the reactive responses when the CHW or research team checks for drug compliance. Percentage of administrations causing adverse reactions will be calculated as the number of adverse reactions detected divided by the number of administrations in the health center catchment. Risk factors for adverse reactions such as age and sex will be examined as needed. The key to managing side effects and potential adverse events (AEs) and serious AEs (SAEs) is through thorough training of CHWs, health facility staff and supervisors, and intensive sensitization of the community. CHWs will monitor their respective communities for AEs and refer any potential SAEs to designated health facilities. Health workers at these facilities will be informed of the program, potential side effects, and provided with AE reporting forms (Appendix 13). Cases that cannot be treated at health centers will be referred to nearest district referral centre or district hospitals, with transport provided by the study.

Any and all potential AEs following treatment with DHAP will be recorded through passive case detection at all local public and private health facilities in the target areas, including referral by CHWs. A data safety monitoring board (DSMB) will be established to oversee and report on any AE and SAEs that are potentially linked to the administration of DHAP, and as outlined in further detail in Section 3.2. The following steps will be taken for all SAEs that present to health facilities:

1. The health facility will complete an AE description form (Appendix 13). The completed form will then be submitted to the DSMB, study coordinator and principal investigator within 72 hours from the identification of the AE/SEA.
2. The DSMB will complete an AE investigation form (Appendix 14) to a) assess if the event is an SEA, and 2) to determine if the AE/SEA was caused by the administration of DHAP as part of this study within 24 hours.
3. The DSMB will provide the completed AE investigation form to the PI, who will submit to the Research Ethics Committees (RECs) at UNZA and PATH. The respective RECs will be notified within 24 hours of the DSMBs completion of the AE investigation form for events determined to be SEAs, and within 48 hours of DSMB notification if deemed an AE, but not an SEA.

Our proposed strategy to reduce risks associated with DHAP in pregnancy (first trimester) include:

- Before providing any woman of reproductive age (12-49) with DHAP we will first ask women if they are pregnant or potentially pregnant
- If a woman reports being pregnant, to determine the trimester of the pregnancy, in addition to asking how many months pregnant she may know she is, she will be asked about the date of her last menstruation and, if necessary, if quickening has occurred (i.e. if she has felt the baby move inside of her)
- To offer women that are unsure of their pregnancy status or who are potentially pregnant a rapid pregnancy test to confirm pregnancy or not
- To clearly explain to women the potential risk of taking DHAP during the first trimester of pregnancy and allow them to opt out of receiving DHAP while still receiving the standard of care in Zambia (the RFTAT intervention)

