# Research Plan

## Study Design

The study design will be a cluster randomized trial comparing an enhanced strategy for malaria elimination (RFDA with DHAP) with the current strategy (RFTAT with AL). Impact evaluation will consist of: 1) community-based, cross-sectional measurement of malaria seropositivity in children aged ≥ 1 month and < 15 years through a random sample survey at the end (two years) of the intervention period; 2) longitudinal follow-up of a subset of individuals participating in reactive responses by a research team; and 3) detection of incident malaria cases and total outpatient attendance at health centers and health posts.

A total of sixteen health centers will be targeted in this RCT (Table 1). The proposed areas were selected from the 11 districts within Southern Province, Zambia that have successfully implemented RFTAT surveillance with the following criteria: a mean monthly incident malaria case load of < 25 and a mean test positivity during ongoing RFTAT of at least 5%. Where multiple health centers fulfilled the inclusion criteria, preference was given to those that are geographically close to one another (minimum 5km buffer to reduce contamination) and are accessible all year round. Selected health centres will be randomized to either control or intervention arms, with 8 health centers per arm (Figure 3).

| Organisation Unit | Confirmed Cases of Malaria (Sep ’13 – Aug ’14) | | | | Positivity Rate (%) during RFTAT |
| --- | --- | --- | --- | --- | --- |
|  | Clinic | Community | Total | Average cases per month |  |
| Chisekesi Rural Health Centre | 176 | 77 | 253 | 21 | 9.4 |
| Habulile Rural Health Centre | 133 | 109 | 242 | 20 | 9.3 |
| Katombora Health Post | 123 | 78 | 201 | 17 | 12 |
| Kazungula Health Post | 71 | 20 | 91 | 8 | 7.9 |
| Keemba Rural Health Centre | 58 | 89 | 147 | 12 | 6.8 |
| Mayoba Rural Health Centre | 46 | 37 | 83 | 7 | 9.4 |
| Moonde Rural Health Clinic | 0 | 214 | 214 | 18 | 8.3 |
| Mubanga Rural Health Centre | 77 | 139 | 216 | 18 | 5.3 |
| Mukwela Rural Health Centre | 86 | 157 | 243 | 20 | 7.8 |
| Munkolo Rural Health Centre | 42 | 76 | 118 | 10 | 6.9 |
| Musokotwane Health Post | 38 | 53 | 91 | 8 | 8.2 |
| Muzya Rural Health Centre | 40 | 83 | 123 | 10 | 9.9 |
| Nadezwe Rural Health Centre | 58 | 107 | 165 | 14 | 11.2 |
| Namwianga Urban Health Centre | 56 | 140 | 196 | 16 | 5.2 |
| Ngwezi Rural Health Centre | 11 | 169 | 180 | 15 | 8.3 |

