| Pangwe Rural Health Centre | 21 | 127 | 148 | 12 | 19.2 |
| Siachitema Rural Health Centre | 14 | 119 | 133 | 11 | 7.4 |
| Simooya Rural Health Centre | 142 | 40 | 182 | 15 | 8.7 |
| Zambia National Service Rural Health Centre | 78 | 40 | 118 | 10 | 10.7 |
| ZCA Rural Health Centre | 215 | 47 | 262 | 22 | 8.3 |

Table 1 – Proposed selected health centre catchment areas along with data from these facilities for the last year.

**Control Arm** - PCD at health centers and health posts, with RFTAT in response to RDT confirmed incident malaria cases as currently outlined in the Step D protocol (Appendix 1). RFTAT consists of screening all individuals within 140 meters of an incident malaria case using a RDT and treating those testing positive with AL.

**Intervention Arm** - PCD at health centers and health posts, with RFDA in response to RDT confirmed incident malaria cases. RFDA consists of treating all individuals within 140 meters of an incident malaria case with DHAP.

[figure not shown]

Figure 3 - Schematic showing control and intervention arms proposed at the health center catchment level. PCD, passive case detection; RFTAT, reactive focal test and treat; RFDA, reactive focal drug administration; AL, artemether-lumefantrine; DHAP, dihydroartemisinin-piperaquine.

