### Research Response

In order to assess parasite clearance and the risk of re-infection following a reactive response, a subset of index cases will be randomly selected for follow-up by a research team within each participating health center catchment area (Figure 7). Equal numbers of index cases will be randomly selected in each arm and in each clinic, with a minimum of two index cases per month in each arm i.e. minimum of four total per month. Only index cases reporting no history of travel will be enrolled. A questionnaire will be administered to all individuals participating in the reactive research responses and a finger prick blood sample will be obtained to collect dried blood spots (DBS) for study research purposes only. Participants will be adequately protected with risks minimized as much as possible during sample collection (see Section 3.1 for more information). Information collected through the questionnaire will include demographic information, current symptoms, recent malaria history, travel history, RDT result, HS RDT result (in RFDA arm only) and treatment administered (Appendix 6 and Appendix 7). Geocoordinates will be collected for each household targeted for a reactive response. Blood samples will be used to detect asexual stage parasites by PCR and all positive samples will be genotyped using a molecular bar code.

Follow-up visits will be conducted 3 (Appendix 9), 30 (Appendix 10) and 90 (Appendix 10) days after the initial reactive response. Additional information will be collected from each targeted individual on signs and symptoms of malaria, other treatments received, adherence to the drugs given (if any), and adverse reactions. A finger prick blood sample will be collected from each individual as a DBS at the 30 and 90 day follow-up visits. From the initial reactive response visit, blood samples will be used to detect asexual stage parasites by PCR and all positives genotyped using a molecular bar code.

For research responses enrolled in the RFDA arm, consenting individuals will be tested using the HS RDT as well as the standard RDT. No treatment decisions will be made based on the results from either the HS RDT or the standard RDT, rather they will all be offered DHAP. Individuals who do not consent to be enrolled in the RFDA arm will continue to receive the standard of care i.e. testing with a standard RDT and if positive, treatment given according to national policy.

[figure not shown]

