## Data and safety monitoring plan

An independent data safety monitoring board (DSMB) will be established consisting of at least 5 independent experts in malaria control, diagnosis, case management, biostatistics and epidemiology and one member of the research team who will receive monthly reports of adverse events during the intervention period of the trial. The charter will include trial stopping rules for safety. No data on futility or benefit will be determinable during the course of the trial as seasonality of malaria transmission timing of outcome data collection preclude developing stopping rules based on outcome data collected during the duration of the implementation of the intervention. Safety concerns associated with the wide scale use of DHAP, although unexpected, will form the basis of development of a stopping rule. The stopping rules for this trial will be based on detection of a significantly higher rate of mortality, hospitalization for possible drug related events, or any other severe adverse event in the RFDA intervention arm compared to expected rates in the control group.

In addition to the DSMB, a regional monitor will be used for supervision of study progress and adverse events. A study pharmacist from the provincial health office will also be used to manage and account for the supply of DHAP used in the study.

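### Section 3.1 fixes one adverse-reaction percentage per administration for both arms, but AL goes only to RDT-positive people and DHAP to all residents in the radius, so the two figures are not comparable

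*Protocol*

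**What the plan says.** Section 3.1 of the protocol says that "Adverse reactions to both RFTAT with AL and RFDA with DHAP will be assessed 3 days following the reactive responses", at the visit where the CHW or research team checks compliance. The measure follows: "Percentage of administrations causing adverse reactions will be calculated as the number of adverse reactions detected divided by the number of administrations", taken by catchment. Age and sex are named as factors to look at if needed; infection status is not. No rule is given for attributing a day-3 event to the drug.

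Section 2.1 defines who is dosed. On the control side the text reads "RFTAT consists of screening all individuals within 140 meters of an incident malaria case using a RDT and treating those testing positive with AL". By contrast, for the other arm it reads "RFDA consists of treating all individuals within 140 meters of an incident malaria case with DHAP".

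Section 3.2 sends monthly adverse-event reports to the DSMB. It bases stopping on deaths, possibly drug-related admissions, or "any other severe adverse event in the RFDA intervention arm compared to expected rates in the control group". No denominator is stated there.

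Section 2.4.1 describes the research responses. RDT results are recorded in both arms; in the RFDA arm "consenting individuals will be tested using the HS RDT as well as the standard RDT". On day 3 each targeted person is followed, dosed or not, and malaria symptoms and adverse reactions are listed as separate items.

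**The concern.** The denominator is conditioned on a positive test in one arm and not in the other, so randomisation does not make the two sets of recipients alike. Fever or vomiting from malaria can occur in most AL recipients but in only a minority of DHAP recipients. The word 'causing' would label any such event that is detected as a drug effect.

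There is a second, separate problem. The safety cost specific to RFDA is that a drug is given to residents who test negative, or would. A rate per administration cannot show that cost, because undosed residents of control foci appear nowhere in it. What is at stake is whether the trial's one defined reaction rate can inform a judgement on net harm to the people reached.

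**Working it through.** The protocol states no adverse-reaction rate, so there is no figure of its own to reproduce.

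**Inputs from the protocol**
- RDT positivity during RFTAT (Table 1, 20 listed facilities, of which 16 are to be used): the sum is 180.2, so the unweighted mean is 180.2/20 = 9.01%. The range is 5.2% to 19.2%.
- Infections missed by test: up to 80% (section 1.3, for microscopy, with the RDT described as similar).
- Test accuracy used for illustration in section 2.14.1: sensitivity and specificity 95% each.
- People in reactive responses: about 30,000. Research subset: about 9,000 (project summary).

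**Assumptions**
- r = true drug-reaction rate, taken as 5% for both drugs.
- s = share of infected people whose malaria symptoms are recorded as reactions.
- Everyone eligible is dosed and seen on day 3.
- The two arms are of equal size.

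**Step 1. Infected share of recipients (π)**
- (a) RDT taken at face value: AL 100%, DHAP 9.0%.
- (b) 80% of infections missed: AL 100%, DHAP 9.01/0.20 = 45%.
- (c) 95%/95% accuracy: prevalence = (0.0901 − 0.05)/0.90 = 4.5%. Positive predictive value = 0.95 × 0.0446/0.0901 = 47%. So AL 47%, DHAP 4.5%.

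The recipients differ in infection status in all three cases.

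**Step 2. Effect on the stated percentage.** Observed rate = r + s × π for each drug, so the spurious gap, AL minus DHAP, is s × (π_AL − π_DHAP).

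| s | (a) gap | (b) gap | (c) gap |
|---|---|---|---|
| 0% | 0 | 0 | 0 |
| 2% | 1.8 points | 1.1 | 0.9 |
| 10% | 9.1 points | 5.5 | 4.3 |
| 30% | 27.3 points | 16.5 | 12.8 |

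In case (a) with s = 10%, AL reads 5 + 10 = 15.0% and DHAP reads 5 + 10 × 0.0901 = 5.9%, although the drugs are equal.

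**Step 3. Is the direction fixed?** Suppose instead that DHAP truly causes reactions in 10% and AL in 5%, and that 5% of uninfected people report symptoms anyway.
- Symptoms in 20% of infected people: AL = 20 + 5 = 25.0%. DHAP = 0.0901 × 20 + 0.9099 × 5 + 10 = 16.4%. Ratio 0.65.
- Symptoms in 5% of infected people: AL = 5 + 5 = 10%. DHAP = 5 + 10 = 15%. Ratio 1.5.

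The same true ratio of 2 can appear on either side of 1, depending on a symptom rate that the protocol does not give.

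**Step 4. Burden per resident reached, with s = 0 and r = 5% for both drugs**
- Stated percentage: 5% in both arms.
- RFTAT per resident: 0.0901 × 5% = 0.45% (0.26% at 5.2% positivity, 0.96% at 19.2%).
- RFDA per resident: 5%.
- Difference: 4.55 points, a factor of 5/0.45 = 11, which the stated percentage does not show.

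**The case against.** The strongest reply is that no comparison is planned. Section 3.1 defines a percentage by catchment and names no contrast between arms, and safety is not among the aims. The stopping rule in section 3.2 compares arms on deaths, admissions and severe events, not on day-3 symptoms. Choosing safety contrasts is commonly left to the SAP. This stands: the absence of a comparison is not the fault. The fault is that one measure with one denominator is fixed for both arms, under a causal label, with nothing to warn against reading it across arms.

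A reader might infer that malaria symptoms will be counted as AL reactions and that DHAP will therefore look safer than it is. The documents do not support that as fact. The numerator is adverse reactions, and the research visits list malaria symptoms separately, so misclassification is a risk and not a rule. People found by community screening may have few symptoms, which makes s small. Passive capture of adverse events and DSMB causality review are stated for DHAP only, which pushes the other way if such events enter the numerator. The direction is therefore open. The separate items do not remove the risk either: they are described for research responses only, most responses are by a single CHW, and section 3.1 draws on both.

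A reader might also infer that the DSMB will be reassured by this percentage. Nothing says it will be used for stopping.

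Finally, the number of administrations is itself counted, so the larger exposure under RFDA is not concealed. But reactions per resident can be recovered only if the undosed residents are also counted and followed.

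**Conclusion.** The point holds as a weakness of the measure, at moderate severity. It rests on two facts in the protocol: who receives each drug, and one rate per administration for both arms with no split by infection status. Read side by side, the two percentages are confounded by infection status. The size and net direction of that confounding cannot be determined from the documents; the gaps of 0 to 27 points above come from assumed symptom rates.

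The denominator problem does not depend on any misclassification. With an assumed 5% reaction rate for either drug, full uptake and Table 1 positivity, it is 0.45% against 5% of residents reached. The 5% is illustrative, but the factor of about 11 depends only on positivity and full uptake when the two reaction rates are equal.

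**What to change.** In section 3.1:
- Keep the per-administration percentage as a description within each drug, counted by the drug actually given, since people in the RFDA arm who do not take DHAP may receive AL.
- Replace 'causing' with 'followed by'.
- State that the figure is not a between-arm comparison.

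For the between-arm comparison, use the research responses. Report adverse events per enrolled resident by randomised arm, dosed or not, with the same capture in both arms and an analysis that allows for clustering by health center. Add two supporting contrasts: RDT-positive residents (DHAP v AL) and RDT-negative residents (DHAP v untreated).

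The cost is protocol wording and additional safety tables from data already planned. The main drawback is precision. About 9,000 people, or 4,500 per arm if split equally, gives roughly 0.0901 × 4,500 = 405 RDT-positive and 4,095 RDT-negative residents per arm, against up to about 15,000 DHAP recipients in all responses. Rare events are therefore estimated less precisely, and the reporting of serious events from all responses should stay as it is. Research responses also exclude index cases with a travel history, and residents know whether they were dosed, so the RDT-negative contrast remains open to reporting bias.
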